# A cluster randomised controlled trial, process and economic evaluation of quality improvement collaboratives aligned to a national audit to improve the care for people with diabetes (EQUIPD): study protocol

**DOI:** 10.1186/s13012-023-01293-0

**Published:** 2023-08-31

**Keywords:** Audit and feedback, Quality Improvement Collaborative, Diabetes, Insulin pump, Randomised controlled trial

## Abstract

**Background:**

People with type 1 diabetes and raised glucose levels are at greater risk of retinopathy, nephropathy, neuropathy, cardiovascular disease, sexual health problems and foot disease. The UK National Institute for Health and Care Excellence (NICE) recommends continuous subcutaneous ‘insulin pump’ therapy for people with type 1 diabetes whose HbA1c is above 69 mmol/mol. Insulin pump use can improve quality of life, cut cardiovascular risk and increase treatment satisfaction. About 90,000 people in England and Wales meet NICE criteria for insulin pumps but do not use one. Insulin pump use also varies markedly by deprivation, ethnicity, sex and location. Increasing insulin pump use is a key improvement priority.

Audit and feedback is a common but variably effective intervention. Limited capabilities of healthcare providers to mount effective responses to feedback from national audits, such as the National Diabetes Audit (NDA), undermines efforts to improve care. We have co-developed a theoretically and empirically informed quality improvement collaborative (QIC) to strengthen local responses to feedback with patients and carers, national audits and healthcare providers. We will evaluate whether the QIC improves the uptake of insulin pumps following NDA feedback.

**Methods:**

We will undertake an efficient cluster randomised trial using routine data. The QIC will be delivered alongside the NDA to specialist diabetes teams in England and Wales. Our primary outcome will be the proportion of people with type 1 diabetes and an HbA1c above 69 mmol/mol who start and continue insulin pump use during the 18-month intervention period. Secondary outcomes will assess change in glucose control and duration of pump use. Subgroup analyses will explore impacts upon inequalities by ethnicity, sex, age and deprivation. A theory-informed process evaluation will explore diabetes specialist teams’ engagement, implementation, fidelity and tailoring through observations, interviews, surveys and documentary analysis. An economic evaluation will micro-cost the QIC, estimate cost-effectiveness of NDA feedback with QIC and estimate the budget impact of NHS-wide QIC roll out.

**Discussion:**

Our study responds to a need for more head-to-head trials of different ways of reinforcing feedback delivery. Our findings will have implications for other large-scale audit and feedback programmes.

**Trial registration:**

ISRCTN82176651 Registered 18 October 2022.

**Supplementary Information:**

The online version contains supplementary material available at 10.1186/s13012-023-01293-0.

Contributions to the literature
Theory and policy recommend increasing the quality improvement capabilities of audit and feedback recipients.We will test a theory-, evidence-, and stakeholder-informed Quality Improvement Collaborative (QIC) to enhance recipients’ capabilities to respond to the National Diabetes Audit.We will evaluate the effect of QIC on the use of insulin pumps, equity of uptake, patient outcomes and cost-effectiveness, as well as explore implementation and engagement with the QIC.Identifying target practices for recipients of feedback from audits, and how to implement these, offers the opportunity for improvements in care and valuable learning to national audit commissioners and providers, and implementation researchers.

## Background

Over 192,000 people in England have type 1 diabetes, almost half of whom have HbA1c levels above 69 mmol/mol putting them at greater risk of retinopathy, nephropathy, neuropathy, cardiovascular disease, sexual health problems and foot disease [1]. The UK National Institute for Health and Care Excellence (NICE) recommends continuous subcutaneous insulin infusion ('insulin pump') therapy for people with type 1 diabetes whose HbA1c is above 69 mmol/mol despite receiving a high level of care [2].

Insulin pump use can improve quality of life [3], reduce cardiovascular risk [4], and increase treatment satisfaction [5]. Yet the National Diabetes Audit (NDA) demonstrates slow and unequal progress in uptake of insulin pumps; around 90,000 people who meet NICE criteria are not prescribed insulin pumps (NDA) [6]. Pump use varies markedly by locality (2% to 47%; [1]), by deprivation (16.3% most deprived; 23.8% least deprived; [1]) and by ethnicity [7]. The NDA has identified accelerating the uptake and equality of insulin pump use as a key priority in reducing mortality and morbidity [1].

The NDA is one of around 60 national audits in England [8]. Funded by the National Health Service (NHS) in England and Wales, it provides feedback on recommended processes of care (e.g. proportions of people with diabetes having foot checks) and attainment of treatment goals (e.g. blood sugar or blood pressure control) to specialist teams. Feedback from the audit highlights areas for improvement to stimulate change. Whilst audit and feedback has shown modest improvements on care delivery [9], there are considerable opportunities to improve the impact of national audit programmes such as the NDA by, for example, incorporating goals and action plans for change [10]. However, a common challenge amongst those leading national audits is that even well-designed feedback may only have limited impact in the absence of robust local quality improvement arrangements. For example, we found no improvements in care from enhanced feedback reports in two trials embedded within a national audit programme which aimed to reduce inappropriate blood transfusions; a major reason for the absence of any improvement was the lack of effective local responses to feedback [11]. Evidence (e.g. [12, 13]), theory [14] and stakeholder prioritised hypotheses [15] highlight an opportunity to increase the effectiveness of national audits by enhancing the ability of feedback recipients to mount concerted quality improvement efforts.

The Healthcare Quality Improvement Partnership (HQIP), the main commissioner of national audits in England, states that, “health care providers require additional support to make best use of performance feedback data. This is likely to be most effective as part of a coordinated regional or national improvement programme” [12]. Several frameworks propose that significant improvements in care can only be achieved by launching and coordinating quality improvement efforts across all levels of healthcare systems (national, organisational, team, and individual) [16, 17]. Whilst national audit may provide the impetus for change at clinical team and individual levels, there is often insufficient local organisational capability to enable change by, for example, systematically aligning actions to barriers to, and levers for, improvement [14]. Local quality improvement may also be undermined by a lack of motivation to change [14, 16, 18], limited opportunities for improvement actions [16, 19] and poor adaptability to local organisational context [20]. HQIP guidance states “national clinical audits need to be put into the local context to inform action plans addressing areas where quality improvements can be made” (p8; [12]).

We have developed a quality improvement collaborative (QIC) that supports providers to improve by selecting actions tailored to local contexts and generating organisational commitment for change [19]. Intervention development [21] included multi-method co-design to understand current responses to national audits and further co-design of a stakeholder-, theory- and evidence-informed intervention to support recipients.

We have explored the feasibility, acceptability, appropriateness and fidelity of this intervention when delivered with two national audits (NDA and National Audit of Dementia [19]). We recently delivered the intervention to 28 diabetes teams and evaluated feasibility, appropriateness, fidelity and scalability. We found that the behaviour change techniques [22] identified in the manual were delivered by facilitators. There was evidence for fidelity of enactment of target behaviours. Participants reported positive attitudes towards the intervention and that the intervention was appropriate [19]. We consider that the intervention is now ready for a definitive effectiveness evaluation.

We will evaluate the effectiveness of NDA feedback with QIC compared to NDA feedback alone, understand intervention implementation, engagement, fidelity and tailoring of actions, and estimate value for money of NDA feedback with QIC.

## Methods

### Study design

EQUIPD (Evaluation of Quality Improvement for People with Diabetes) is an efficient cluster randomized controlled trial with parallel process and economic evaluations using routine NDA data. One hundred twenty specialist diabetes teams (clusters) will be allocated on 1:1 basis to either control (NDA feedback alone) or intervention (NDA feedback plus QIC) arms (Fig. 1). Control arm teams will receive the intervention after the study follow-up period, but prior to completion of data analysis.

**Fig. 1 Fig1:**
[figure not shown]
CONSORT flow chart

### Study setting

Specialist diabetes teams from England and Wales providing care in community and in-patient settings. These multidisciplinary teams include diabetologists, endocrinologists, diabetes specialist nurses and dieticians.

### Cluster eligibility

Specialist diabetes teams which accept an invitation to participate in the QIC will be eligible.

### Patient eligibility

Our patient population will be all people identified through the national audit before the intervention period (baseline) with an HbA1c level above 69 mmol/mol and not prescribed insulin for a pump in the previous year.

### Randomisation and blinding

Participating specialist teams will be randomised after agreement to participate and confirmation of eligibility. Specialist diabetes teams (clusters) will be independently randomised on a 1:1 basis to receive the intervention or waitlist only control (receiving the intervention after the trial follow-up period ends), using a computer-generated minimisation programme.

Minimisation factors: Baseline proportion moving onto a pump in the 15 months prior to the intervention period (above or below median); size of target patient population in specialist team (above or below median); previous QIC pilot participation [19] (yes or no).

Participating specialist teams will not be blinded to allocation.

### Intervention

Teams allocated to the intervention arm will receive standard NDA feedback (described in Supplementary materials 1) and the QIC to promote the uptake of insulin pumps.

The QIC will be delivered through two virtual workshops (6 h in total), two virtual outreach sessions (30 min) and virtual facilitated multisite meetings (1 h each). Delivery will be by the NDA Quality Improvement Lead, the DiabetesUK Engagement Lead, the NDA Clinical Lead and clinicians with expertise in improvement and insulin pump use. The intervention will be delivered virtually via Microsoft Teams and Google JamBoard.

We will ask participating teams to attend workshops and ensure a team member attends at least 8 of the 12 multisite meetings. Teams are supported over a 15-month period. Only identified, invited members from participating sites will have access the virtual workshops and meetings. Delivery will be in three parallel cohorts of 20 teams, with each cohort forming a ‘collaborative.’ Learning will be shared between cohorts by the facilitator. Teams will be asked to identify a replacement if any team member leaves. The replacement will be offered a 30-min one-to-one call to support within-team discussions about the intervention.

The logic model (Fig. 2) outlines the behaviours targeted by the intervention. It also describes the mechanisms that influence their implementation and the behaviour change techniques intended to address these mechanisms.

**Fig. 2 Fig2:**
[figure not shown]
EQUIPD Protocol

Intervention content and delivery are described in the TIDieR framework [23] (Appendix) and logic model (Fig. 2) and an intervention manual. In summary, the intervention supports teams to specify a goal; analyse influences upon care; link influence to the improvement action; collaborate; review feedback; engage stakeholders; link the work to priorities; and consider existing work. We anticipate that enactment of these target behaviours will provide the informational appraisal to select effective actions and generate organisational commitment needed to bring about those actions.

### Follow-up

We have chosen an 18-month follow-up period for two reasons. First, it reflects the duration of the QIC, plus 3 months to assess sustainment. Second, it allows for a period for teams engaging with the QIC to consider, plan and initiate changes in clinical practice.

All teams will be given the opportunity to receive the intervention alongside standard NDA feedback. It is not possible to support all teams at once. We will therefore randomly allocate half to receive the intervention, whilst the other half will receive the intervention 18 months later (control group) 3 months after intervention arm delivery is completed. Teams that choose not to be included in the evaluation will receive the intervention alongside the control group.

Allocation concealment is not feasible in this trial. We will maintain a log of those unblinded to allocation. This will include the intervention delivery team and those research team members who need to know allocations to undertake the study. The intervention supports teams to engage local patients to identify potential barriers and actions to improvement, as such patients may not be blinded to involvement in the intervention arm.

### Study procedure

Each cluster will be a clinical team providing specialist care to adults with diabetes, as identified by NHS Digital. Specialist teams will be invited both to be part of the QIC and to participate in the evaluation by the NDA.

We plan to recruit 60 specialist teams per arm, each including an average of 600 patients with type I diabetes with HbA1c > 69 mmol/mol not using a pump within the previous year.

Sample size calculation and the assumed intra-class correlation co-efficient (ICC) is described in Supplementary materials 1.

### Recruitment

Clinical leads will give consent on behalf of their specialist diabetes teams. As part of usual care, the NDA will email all specialist teams to invite participation in the QIC. The invitation will describe the evaluation and ask whether they, as a team, wish to be included in the evaluation. Further recruitment and withdrawal procedures are described in the Supplementary materials 1.

### Primary and secondary outcomes

The primary outcome is the proportion of adults with type 1 diabetes and raised glucose levels (HbA1c above 69 mmol/mol) starting and continuing to use insulin pumps for at least 3 months within an 18-month follow-up period.

Our secondary outcomes are:Change in blood glucose levels as measured by HbA1c in people with type 1 diabetes and raised glucose levels between the latest measurement in the 12 months preceding the start of the intervention and the latest measurements recorded during the study period.Any record of insulin pump prescribing, including for periods shorter than 3 months.Insulin pump use sustained over at least 6 months.

### Data collection

Trial outcomes and demographic data will be assessed using routinely collected individual patient data already extracted for the NDA. A statistician embedded within the NDA team at NHS England (previously NHS Digital) will analyse individual patient-level data with supervision from a researcher experienced in using NDA data and by the senior trial statistician. Supplementary materials 1 details data extraction.

From the audit data, we will define a closed cohort of participants who have an HbA1c level above 69 mmol/mol and were not prescribed insulin for a pump in the previous year.

Data will be summarised on the number of specialist teams invited to participate, agreed to participate, and are randomised. For randomised clusters, based on data from the NDA, we will summarise the baseline proportion of patients moving onto a pump in the 15 months prior to the intervention period and the size of target patient population in specialist team. We will also summarise the number and proportion of teams who previously participated in the QIC pilot. The target patient population will be people with an HbA1c level above 69 mmol/mol and not prescribed insulin for a pump in the previous year. We will summarise the age, sex, ethnicity and deprivation of patients. We will extract data from the 15 months prior to randomisation and the 18 months following randomisation.

For the intervention sessions, data will be collected on the timing, mode of delivery and duration of each session. Data will also be collected on the attendance at each session (by team and job title). Intervention content will be assessed as described in the fidelity assessment. Participant engagement will be assessed as described in the process evaluation.

All patient-level data will come from the NDA.

### Data monitoring

The NDA validates, monitors and reports the quality of patient outcome and demographic data [24]. Data regarding randomization will be monitored for quality and completeness by the clinical trials unit, using established verification, validation and checking processes.

### Data analysis

We will use all available data from all randomised specialist teams, according to a detailed pre-specified plan finalised and agreed by the research team before any analyses are undertaken. We will conduct all analyses on the intent-to-treat (ITT) population, including all specialist teams and patients in the group they are randomised to regardless of intervention adherence.

We will conduct a single final analysis after the end of the follow-up period, when fully cleaned data are available from the NDA. Blinded interim reports will be presented to the Project Steering Committee (PSC) containing descriptive information on site recruitment and intervention adherence.

### Summary of intervention data

Quantitative summaries of intervention delivery will be presented, including timing and mode of delivery of sessions, uptake and engagement.

Summary statistics will be presented for baseline data by treatment group using means, standard deviations, medians, minimum, maximum, and quartiles for continuous variables, and counts and percentages for categorical variables. Summaries will be presented at the specialist team level where appropriate.

We will compare characteristics of patients lost to follow-up with those not lost to follow-up to assess for attrition bias.

### Primary outcome analysis

The primary ITT analysis will compare the primary outcome between trial arms, using mixed effects logistic regression, with patients nested within specialist teams, and with specialist teams treated as a random intercept, adjusting for patient-level and team-level covariates (including patient age, sex, ethnicity, deprivation and team-level stratification factors). Estimated mean odds ratios will be reported with 95% confidence intervals, *p* values and intra-cluster correlation coefficients.

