### Secondary outcome analysis

For binary secondary outcomes (any insulin pump prescribing, sustained insulin pump prescribing), mixed effects logistic regression will be used, using the same approach as for the primary outcome.

For continuous secondary outcomes (glucose levels measured by HbA1c), we will use mixed effects linear regression and report estimated mean differences with 95% confidence intervals, *p* values and intra-cluster correlation coefficients.

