### Study progress

We have gained ethical and Health Research Authority approval. We have recruited and allocated 77 clusters, where a cluster includes up to 3 specialist teams within an organisation or patient pathway. This is the majority of diabetes specialist teams in England and Wales. More recent NDA data suggests that the control group may improve by 2%, rather than the estimated 3% figure used in our initial power calculations.

Although our actual recruitment figure is lower than planned (*n* = 120 teams), 77 clusters will allow us to detect an absolute increase of 8% in prescribing of insulin pumps (i.e. 2% in control arm versus 10% in intervention arm) whilst retaining 87% power. This assumes a parallel design without baseline measures. Therefore, after adjusting for baseline, the power should increase beyond what is estimated above. We therefore believe that our trial is sufficiently powered to detect a clinically important improvement. We have discussed this with our independent Project Steering Committee (Supplementary materials 1) who agree with this assessment.

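### The primary model's only random intercept is on the specialist team, but the allocated units are 77 clusters of up to three teams; read literally, this omits the randomised level

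*Protocol article*

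**What the plan says.** The design sections of the protocol article treat team and cluster as the same thing. Study design plans 120 specialist teams, labelled as clusters. Randomisation and blinding says "Specialist diabetes teams (clusters) will be independently randomised on a 1:1 basis". Study procedure says "Each cluster will be a clinical team providing specialist care to adults with diabetes", and continues: "We plan to recruit 60 specialist teams per arm, each including an average of 600 patients".

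Study progress reports something different for the trial as carried out: "We have recruited and allocated 77 clusters, where a cluster includes up to 3 specialist teams within an organisation or patient pathway". The revised power statement in that section rests on the 77 clusters: "2% in control arm versus 10% in intervention arm) whilst retaining 87% power".

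The Primary outcome analysis section keeps the team as its only random effect: "with patients nested within specialist teams, and with specialist teams treated as a random intercept". It also adjusts for team-level stratification factors and reports intra-cluster correlation coefficients. For the binary secondary outcomes, Secondary outcome analysis says "mixed effects logistic regression will be used, using the same approach as for the primary outcome". For HbA1c it specifies mixed effects linear regression without naming the level of the random effect.

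**The concern.** In a cluster randomised trial the model has to represent the unit that was allocated. By the description in Study progress, teams in one cluster belong to one organisation or patient pathway and receive one joint allocation. A model with patients nested in teams, and nothing above the team, treats such teams as if each had been allocated separately. Where their outcomes are correlated, it overcounts the independent units and understates the standard error of the treatment effect.

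With several hundred patients per unit, precision depends mainly on the number of independent units, so the choice of level matters for the primary test. The error has one direction: confidence intervals too narrow, and too high a chance of concluding that the collaborative works when it does not. The analysis would also count different units from the power statement, which counts clusters.

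**Working it through.** **Inputs from the article.** 77 allocated clusters of one to three teams; 1:1 allocation, taken as 38 versus 39; planned average of 600 patients per unit; 2% versus 10%; stated power 87%; 95% confidence intervals, so two-sided 5% is assumed.

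**Not in the article.** The ICC (deferred to the supplement), the number of teams in the 77 clusters, and the share *s* of between-team variance that lies at cluster level. The last two are assumed below and varied.

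**1. The stated power.** Without the ICC, the 87% cannot be reproduced independently; it can only be solved backwards.
- With equal cluster sizes and ICC 0.23, the design effect is 1 + 599 × 0.23 = 138.8.
- Effective sample sizes are 38 × 600 / 138.8 = 164 and 39 × 600 / 138.8 = 169. The two-proportion formula for 2% versus 10% then gives about 87%.
- With an assumed coefficient of variation of cluster size of 0.6, the ICC that gives 87% is about 0.17.
- At ICC 0.23, 120 independently allocated teams (60 × 600 / 138.8 = 259 effective patients per arm) would give about 97%.

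The 87% is therefore compatible with a count of 77 units. This illustrates the difference between the two counts; it does not show that the 87% is wrong.

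**2. Effect of a team-only intercept.** Let *k* be the number of teams in a cluster. With large teams of equal size:
- variance ratio (true / modelled) *R* = 1 + *s* × (Σk² / Σk − 1)
- type I error = 2 × (1 − Φ(1.96 / √R))

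Worked case: 44 clusters of one team, 23 of two and 10 of three.
- Clusters: 44 + 23 + 10 = 77. Teams: Σk = 44 + 46 + 30 = 120.
- Σk² = 44 + 92 + 90 = 226, and 226 / 120 = 1.883.
- *s* = 0.25: R = 1 + 0.25 × 0.883 = 1.22, type I error 7.6%.
- *s* = 0.5: R = 1 + 0.5 × 0.883 = 1.44, type I error 10.3%.

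Other assumed mixes of one-, two- and three-team clusters, same formula:

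| Mix (1 / 2 / 3 teams) | Teams in 77 clusters | Σk²/Σk | s = 0 | s = 0.25 | s = 0.5 | s = 1 |
|---|---|---|---|---|---|---|
| 90% / 8% / 2% | about 86 | 1.25 | 5.0% | 5.7% | 6.5% | 8.0% |
| 60% / 24% / 16% | about 120 | 1.92 | 5.0% | 7.7% | 10.5% | 15.8% |
| one third each | 154 | 2.33 | 5.0% | 9.0% | 12.9% | 19.9% |
| all with three (ceiling) | 231 | 3.00 | 5.0% | 11.0% | 16.6% | 25.8% |

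For the 120-team row the modelled standard error is 0.90, 0.83 and 0.72 of the true one at *s* = 0.25, 0.5 and 1. For the 86-team row it is 0.97, 0.94 and 0.89.

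**3. Check by simulation.** Random-intercept logistic models with a likelihood-ratio test, 77 clusters, 2% event rate, 385 patients per team (77 × 600 / 120), assumed between-team variance 0.8 on the logit scale, no treatment effect, 600 runs per scenario. The Monte Carlo standard error is about 0.9 points at 5%.

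| Teams | Random intercept on | s = 0 | s = 0.25 | s = 0.5 | s = 1 |
|---|---|---|---|---|---|
| about 86 | team | 4.5% | 6.0% | 6.5% | 9.0% |
| about 86 | cluster | 5.3% | 5.3% | 5.7% | 5.8% |
| about 120 | team | 5.0% | 7.7% | 9.3% | 16.0% |
| about 120 | cluster | 4.8% | 5.2% | 4.5% | 6.0% |

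The simulation agrees with the formula. Placing the intercept on the allocated cluster keeps the error close to 5%.

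**The case against.** The strongest reply is that specialist team is simply this article's label for the randomised unit. Study design and Randomisation and blinding use the two words as synonyms. The model section itself adjusts for the factors used in the minimisation and reports an intra-cluster coefficient. Study progress calculates power on 77 units, compares 77 with the 120 originally planned, and says that the steering committee discussed it. All this suggests that the trialists regard the allocated cluster as the unit of inference and that the model text was not updated. On that reading there is no inflation. The detailed analysis plan, which is not shown, may already say so.

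This reading is plausible and cannot be excluded. It does not remove the conflict, because Study progress itself separates the two terms and nothing says that the team in the model is the allocated cluster. An analyst who follows the text as written would fit the wrong level. Nor is this a detail that an article leaves to the analysis plan: the article names the level.

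Four stronger conclusions that a reader might draw are not supported:
- That standard errors will certainly be too small. This needs both the literal reading and correlation between teams in one cluster. A shared organisation or pathway makes correlation plausible, but the article does not quantify it.
- That 120 teams were recruited. 120 was the target; no count of teams within the 77 clusters is given.
- That every secondary outcome is affected. The cross-reference to the primary method covers only the binary ones; the HbA1c model names no level.
- That the 87% power is wrong. It counts the allocated units and cannot be recalculated without the ICC.

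**Conclusion.** The conflict stands and bears on the primary test. The allocated unit in Study progress is a cluster of up to three teams, while the stated model has a random effect for teams only. If that is followed literally and teams in a cluster are correlated, type I error exceeds the nominal 5%.

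The documents do not fix the size. With 25% to 50% of between-team variance at cluster level, it is about 5.7% to 6.5% for about 86 teams and about 7.6% to 10.5% for 120 teams, the latter range spanning the two assumed mixes that give 120. It is nil if the share is zero, and larger if most clusters hold several teams. The figures assume teams of equal size, a normal reference distribution and, in the formula, negligible sampling error within teams. If team was meant as the allocated cluster, the defect is in the wording alone. Either way the text should be settled before analysis.

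**What to change.** State in the primary and secondary outcome models that the random intercept is on the allocated cluster (n = 77). For HbA1c this fills in a level that the article does not name. A further intercept for team within cluster is optional; the inference on the treatment effect needs the allocated cluster. Say that the minimisation covariates and the reported ICC refer to that same unit. Reconcile Study design, Randomisation and blinding, Study procedure and Primary outcome analysis with the cluster definition in Study progress.

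The cost is one model term and a few sentences, with no new data beyond the allocation list. Confidence intervals may be somewhat wider than under a team-only model. If the analysis plan already uses the allocated cluster, only the wording needs correcting.

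### The only baseline-uptake term named for the primary model is a median split, which gives up part of the power gain the article expects from baseline adjustment

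*Protocol article*

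**What the plan says.** The Protocol article, Primary outcome analysis, compares the arms "using mixed effects logistic regression, with patients nested within specialist teams, and with specialist teams treated as a random intercept", and "adjusting for patient-level and team-level covariates (including patient age, sex, ethnicity, deprivation and team-level stratification factors". It does not define the team-level factors there. They are listed under Randomisation and blinding, where the uptake factor is "Baseline proportion moving onto a pump in the 15 months prior to the intervention period (above or below median"; team size is split at its median in the same way, and pilot participation is yes or no. Secondary outcome analysis applies the same approach to the two binary secondary outcomes.

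Under Data collection, the baseline proportion moving onto a pump and the size of the target population are to be summarised for every randomised cluster, so both are held as numbers and not only as categories.

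Study progress reports 77 clusters against 120 planned teams and gives power for "2% in control arm versus 10% in intervention arm" "whilst retaining 87% power". It adds "This assumes a parallel design without baseline measures", and that "after adjusting for baseline, the power should increase beyond what is estimated above". It does not say how large the increase would be or in what form baseline enters the model.

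**The concern.** Patients prescribed insulin for a pump in the previous year are excluded from the cohort, so there is no useful individual baseline value of the outcome. Prior uptake at cluster level is therefore the natural meaning of baseline adjustment here. Between-cluster variation dominates the variance in this trial, so a covariate that predicts follow-up uptake at cluster level is where precision can be gained.

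Two categories are normal for a minimisation programme. Carried into the model, they treat a cluster just above the median like the highest-uptake cluster, and they leave any imbalance within each half unadjusted. What is at stake is efficiency: the article looks to baseline adjustment for extra power while naming baseline only in a form that delivers part of it. Nothing here points to bias, since allocation is random and minimised on this factor.

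**Working it through.** **Inputs from the article.** 77 clusters at 1:1, taken as 38 control and 39 intervention; average 600 patients (Study procedure, planned per team, not restated for the 77 clusters); 2% v 10%; stated power 87% without baseline.

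**Assumptions.** Two-sided alpha 0.05 (from the 95% confidence intervals). The ICC is in the supplement and not shown, so it is back-solved. The correlation r between baseline and follow-up uptake at cluster level is not given, so a range is used.

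**Step 1: the stated 87%.** It cannot be checked directly without the ICC. With design effect DE = 1 + 599 × ICC and SE² = DE × [0.02 × 0.98/(38 × 600) + 0.10 × 0.90/(39 × 600)], an ICC of 0.237 gives DE = 143.0, SE² = 143.0 × 4.706×10⁻⁶, SE = 0.0259. Then 0.08/0.0259 − 1.960 = 1.12, and power is 87%. With a pooled null variance the ICC is 0.230. Varying cluster size from 300 to 1,200 hardly moves it.

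**Step 2: what the split keeps.** A continuous covariate with a linear relation explains r² of the between-cluster variance. Its median split explains r² times the squared correlation between the covariate and its split. For a normal covariate that factor is 2/π = 0.637, a loss of 36%. For other shapes the loss is 25% (uniform), 44% (beta(2,98), mean 2%), 52% (exponential), and 48% to 63% (lognormal, sigma 0.5 to 0.8).

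**Step 3: power, normal covariate.** DE becomes 1 + 599 × 0.237 × (1 − R²), with R² = r² (continuous) or 0.637r² (split). Control is 2% throughout, and SE is recomputed for each effect. Unadjusted power is 87% at 8 points and 59% at 5 points.

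| r | Residual between-cluster variance, split v continuous | SE excess with split | Power at 8 points, split v continuous | Power at 5 points, split v continuous |
|---|---|---|---|---|
| 0.3 | 0.94 v 0.91 | 2% | 88.8% v 89.8% | 62% v 63% |
| 0.5 | 0.84 v 0.75 | 6% | 91.9% v 94.5% | 67% v 71% |
| 0.7 | 0.69 v 0.51 | 16% | 96.0% v 99.0% | 75% v 86% |
| 0.8 | 0.59 v 0.36 | 28% | 97.9% v 99.9% | 81% v 95% |

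With the pooled null variance and its ICC of 0.230, the 5-point figures at r = 0.7 are 75% v 87%.

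**Step 4: detectable effect at 87% power, r = 0.7.** Solve d = (1.960 + 1.126) × SE(d), with SE recomputed at 2% v 2% + d.

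- Split: DE = 98.7 and SE = 0.0200 at d = 0.062, so 6.2 points.
- Continuous: DE = 73.4 and SE = 0.0164 at d = 0.051, so 5.1 points.

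These are design-effect approximations on the proportion scale, not simulations of the planned logistic mixed model.

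**The case against.** The covariate list opens with the word including, so it is not closed. The median cut is given as coding for the minimisation programme, and the model section does not say the same coding is used. A detailed pre-specified analysis plan is announced, and coding is commonly left to it. All of this stands: the article cannot be read as ruling out a continuous term, only as naming none. What remains is that the one form it does fix for this factor is the weaker one, and it says in the same article that baseline adjustment should bring power.

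Three stronger readings are tempting, and the documents do not support them.

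- A reader might infer that baseline adjustment is what justifies 77 clusters. The article's case is 87% power without baseline measures, with any gain as an extra.
- A reader might infer that the claim of higher power is wrong. It gives no size, and in every case above power with the split still exceeds 87%.
- A reader might take a loss of over a third as a property of this trial. It is the result for a normal covariate with a linear relation; the shapes tried give 25% to 63%. A proportion averaging near 2% is plausibly right-skewed, but its distribution is not shown.

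It is also fair to say that the 5-point figures concern an effect the trial does not target. At its own 8-point target, power is near its ceiling and the loss is small.

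**Conclusion.** The point holds as a free or cheap improvement in efficiency. It is not an error in the power statement or a threat to the validity of the primary estimate. At the 8-point target, naming only the median split costs about 1 to 3 points of power for r between 0.3 and 0.8. The cost is material only if the true effect is well below a fivefold rise and prior uptake predicts later uptake fairly strongly: at r = 0.7, about 11 points of power at a 5-point effect, or a detectable effect of 6.2 instead of 5.1 points. At r = 0.3 it is negligible. These sizes rest on an ICC back-solved at about 0.24, 600 patients per cluster, a normal covariate with a linear relation, and an assumed r; none of the ICC, the shape or r is in the article.

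**What to change.** State that baseline uptake enters the primary model and the binary secondary models as a continuous covariate, for example the empirical logit of the baseline proportion, and team size as log size, in place of or alongside the median-split indicators. Keep pilot participation as yes or no. Calculate both at the level of the unit that carries the random intercept, since Study progress says "We have recruited and allocated 77 clusters, where a cluster includes up to 3 specialist teams within an organisation or patient pathway".

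The cost is wording only, because the audit already supplies both quantities. The one downside is that a functional form has to be chosen and fixed before any analysis. If the analysis plan already specifies continuous terms, a sentence saying so settles the point.
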